# Frequency of repositioning for preventing pressure ulcers in patients hospitalized in ICU: protocol of a cluster randomized controlled trial

**DOI:** 10.1186/s12912-021-00616-0

**Published:** 2021-07-05

**Keywords:** Critical care, Pressure ulcers, Bedsores, Nursing, Randomized, Clinical trial, Clusters

## Abstract

**Background:**

Despite being considered preventable, ulcers due to pressure affect between 30 and 50% of patients at high and very high risk and susceptibility, especially those hospitalized under critical care. Despite a lack of evidence over the efficacy in prevention against ulcers due to pressure, hourly repositioning in critical care as an intervention is used with more or less frequency to alleviate pressure on patients’ tissues. This brings up the objective of our study, which is to evaluate the efficacy in prevention of ulcers due to pressure acquired during hospitalization, specifically regarding two frequency levels of repositioning or manual posture switching in adults hospitalized in different intensive care units in different Colombian hospitals.

**Methods:**

A nurse-applied cluster randomized controlled trial of parallel groups (two branches), in which 22 eligible ICUs (each consisting of 150 patients), will be randomized to a high-frequency level repositioning intervention or to a conventional care (control group). Patients will be followed until their exit from each cluster. The primary result of this study is originated by regarding pressure ulcers using clusters (number of first ulcers per patient, at the early stage of progression, first one acquired after admission for 1000 days). The secondary results include evaluating the risk index on the patients’ level (Hazard ratio, 95% IC) and a description of repositioning complications. Two interim analyses will be performed through the course of this study. A statistical difference between the groups < 0.05 in the main outcome, the progression of ulcers due to pressure (best or worst outcome in the experimental group), will determine whether the study should be put to a halt/determine the termination of the study.

**Conclusion:**

This study is innovative in its use of clusters to advance knowledge of the impact of repositioning as a prevention strategy against the appearance of ulcers caused by pressure in critical care patients. The resulting recommendations of this study can be used for future clinical practice guidelines in prevention and safety for patients at risk.

**Trial registration:**

PENFUP phase-2 was Registered in Clinicaltrials.gov (NCT04604665) in October 2020.

## Background

Pressure ulcers (PU) are wounds that affect the skin, caused by prolonged contact or friction in certain points where increased mechanical pressure is applied by the patients’ own weight, especially under skeletal prominence areas (such as the sacrum, trochanters, scapulae, or shoulder blades, heels, and elbows) [1–3]. An increased rate of these events and their complications determine changes in the physical and mental state of the patients and their families, a decreased quality of life level, in addition to higher hospital costs and an increase in healthcare system expenses [1].

The absence of pressure ulcers is considered a quality indicator for installed safety programs and special care given to patients at hospitalization-level risk; therefore, prevention plans for these events should be implemented in patients at a higher risk. Even though considered preventable, PUs constitute between 10 and 50% of adverse events while affecting between 30 and 50% of patients at high and very high risk, especially those hospitalized in critical care services [2, 4]. The incidence of PUs in patients admitted into ICUs varies from 3,3 and 52,9% worldwide [5]. .These patients suffer a diminishing of their natural perception due to the effects of sedation and analgesia required for these services. As a result, a chronic and painful pressure over any area of the body produces little to no reaction in patients for them to change their position.

Among the different factors associated with the emergence of PUs, there is age (OR 2.14 [95% IC 1.27–3.62]), diabetes (OR 5.58 [95% IC 1.58–18.7), duration of MBP < 60-70 mmHg (OR 1.09 [95% IC 1.02–1.17]), mechanical ventilation (OR 23 [95% IC 6.42–86.6]), continuous venovenous hemofiltration or intermittent dialysis (OR 3.7 [IC 95% 1.03–13.86]), use of vasoactive drugs (OR 1.02[95% IC 1.02–1.03]), use of sedatives (OR 1.02 [95% IC 1.01–1.03]) and a low amount of shifts in position (OR 3.63 [95% IC 1.09–12.05]). The information proved that wounds due to pressure and pressure ulcers occur more frequently in patients who are hardly mobilized at lower rates in 24 h (OR 3.63 IC 95% [1.09–12.0]), meaning a repositioning rate of 4 times in 24 h [5, 6]; and a likelihood of 2,96 for grade II pressure ulcers (95% IC 1.23–7.15) [6].

.Within diverse clinical practices for preventing PUs and presenting a higher efficacy, there are anti-decubitus mattresses, the use of gels in surgical patients, genital care in patients with incontinence, and foam bandages in the sacrum region [2, 6]. However, despite its low evidence and no efficacy results, repositioning is also recommended as a prevention strategy.

Repositioning is a nursing care practice utilized for preventing PUs, and its main objective is to reduce mechanical pressure on the skin (which is increased by gravity force) in the aforementioned areas at risk, which is under skeletal prominence areas in patients who completely motionless and in bed rest [7, 8]. Information regarding the impact of repositioning frequency in patients in ICUs has been indirectly obtained from cohort studies and systematic revisions of related literature [9–15].

These studies have reported that the emergence of second and first-degree PUs occurs when a static patient is repositioned at very low rates. This is up to 6 times a day (OR 3.63 IC 95% 1.09–12.0) [5, 6]. However, the precise frequency of repositioning, which would best reduce these wounds’ emergence, remains unknown. The existing evidence reported from systematic revisions of literature on posture shifting’s impact showed a great limitation in pre-existing studies, mainly due to a lack of means and precision to reach valid results [7].

Clinical Practice Guidelines indicate that a patient with an alteration in their state of consciousness should be mobilized frequently every 2 h and that mobilization is better than no mobilization whatsoever [1, 6]. However, levels of information on this recommendation are low according to a Grade evaluation [1, 6]. This implies a lack of evidence on the impact of repositioning in the prevention of PUs.

In addition to this, there is no evidence of possible complications associated with different mobilization frequencies [7]. Studies on routinely preventive interventions, such as the postural shifts and their efficacy in care for patients at high risk for ulcers in ICUs, deserve to be revised carefully. This study aims to solve any uncertainty that exists over what repositioning frequency in static patients best reduces PUs and the possible complications of such interventions. We have planned to perform a pressure ulcer prevention study by nursing in its second phase (PENFUP phase 2). We hypothesize that more frequent repositioning (≤ to every 2 h) performed by nursing staff and critical patients is more effective in reducing the development of pressure ulcers than any other conventional repositioning (applied less frequently ≥ to every 4 h).

Therefore, we have developed a cluster randomized controlled clinical trial that is also multi-centric, pragmatic, and double-blind, made up of two branches comparing a frequent repositioning intervention of 2 h or less with a group of conventional care.

The specific aim is to evaluate the efficacy in preventing PUs acquired during hospitalization on two frequency levels of repositioning or posture shifts in adult patients in different ICUs (clusters) in different regions across Colombia. The three specific aims of this study are 1) to evaluate the efficacy in the intervention of greater frequency, relative to the group of conventional care in the emergence of pressure ulcers and secondary outcomes by clusters; 2) to analyze the hazard ratio (HR) of patients included in the repositioning group of greater frequency compared to the group of patients included in the conventional group in the development of their first PU during their stay in ICUs, and 3) to describe complications related to changes in the position of patients in different ICUs of different hospitals across Colombia.

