### Inclusion and exclusion criteria

Criteria for clusters (ICUs) inclusion: ICUs that admit adult patients (≥ 18 years) in critical condition, with any type of care emphasis (surgical, medical, neurological, or a mixture of any), with a minimum of 10 beds, that submit the feasibility survey and agree to commit to the care assigned in the randomization until including the total number of the sample. At least one ICU will be included from each hospital. In case one hospital may participate with more than one ICU, the units should have to receive the same allocation resulting from the randomization.

Criteria for clusters exclusion: intermediate care units or coronary care units in which patients are self-mobilized; or critical units for burned patients. Also, units destined for the care of patients with Covid 19 in which the standard of repositioning is between every 12–16 h.

Criteria for patient inclusion in each cluster: all patients are eligible as long as they are completely unable to move, have their skin intact at the moment of their admission into the ICU, are care-dependent for their complete mobilization (including unconsciousness, being under sedation or assisted ventilation), and are scheduled for a hospitalization period of at least 48 h.

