### Randomization and blinding

Previous consent to participate will be solicited for the director of each cluster (medical director of the ICU, nursing coordinator of the ICU) and for nursing staff that will perform the intervention.

All the ICUs participants will be randomized (ratio 1:1) to be assigned to either an intervention group (an indication of repositioning every 2 h) or to conventional care (Intervention provided by care providers using a non-standardized frequency of repositioning). The randomization will be set in the main execution center of the study, which is Fundación Cardioinfantil located in Bogotá, and will be computerized with random numbers. Besides, randomization will be executed using a permutation design by blocks of two possible combinations (intervention A or B). The allocation will be openly announced in each hospital. The study will be blind to evaluators (internal analysts and statisticians) [16, 19, 20]. Furthermore, following this, we plan to apply a consent form for the patients [or their parents according to their health status] when admitted to the ICU.

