#### Control group B (conventional care)

The units randomized to this care will be labeled as conventional care will not implement any intervention. Patients in this group will receive the usual care for repositioning applied at any frequency.

Furthermore, patients from both groups will receive all other interventions that are currently applied in their hospitals regarding the prevention of PUs according to their hospital’s protocols. Additionally, repositioning will be performed according to routine practices related to initiation, interruption, re-initiation, or finalization of posture changes, depending on the state of health of each patient, medical orders, and nursing decisions. Patients recruited in each ICU will be follow up when they develop their first PU (stage I), or when they begin the autonomous mobilization [ambulation], or when they are transferred to service to another hospital, or they discharge to their homes, or if they die in the ICU.

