Each center will designate a leader responsible for the PENFUP phase 2 study procedures in each ICU. Each leader must ensure the complete execution of the project day by day and the accurate application of the assigned intervention in each shift. The healthcare staff assigned to group A (high frequency each 2/ h) will receive automatic text messages by cellphone twice a week to remind the intervention frequency to be applied. Leaders from each center will designate two groups of data collectors to operate based on the informed consent given by patients or their families and will gather information of each intervention day bay day in a register format to be completely archived into the study’s platform, including the number of total daily posture shifts per patient in each ICU.

Each center will receive a set of general initiation instructions in person or via teleconference or internet conference. Each center will also receive the investigators’ manual and questionnaires for collecting data to be included in the study’s platform. The total of postural shifts in 24 h will be registered to maintain proper management of the number of shifts per patient calculated for both high and conventional care. Other variables that will be included contain information of each hospital (the type of hospital, total number of nurses, relation nurse-patients, type of prevention protocols for pressure ulcers, and incidence of a pressure ulcer from the year before the beginning of the study); and patient variables (demographic, health history, health status in ICU, complications in ICU, pressure ulcers and location, repositioning complications and reason of ICU discharge) (Table 1).

**Table 1 Tab1:** Variables and timeline for inclusion by each ICU. The complete timeline for each ICU is about 3–4 months

Variables and time to collection 1–4 Months by ICU	Variable to be obtained in each ICU				Type of variable by ICU by Intervention and Control			
**Months 1 to 4**	**T1√**	**T2√**	**T3√**	**T4√**	**T1√**	**T2√**	**T3√**	**T4√**
**1-Primary Outcome**	Development of new pressure ulcers in clusters: ▪ Areas defined of injury: sacrum, heels, ankles, elbows, hip, scapula ▪ Others				Rate ulcers per ICU /total control Rate ulcers per ICU/total intervention Median (IQR).			
	Stage of ulcers: I, II, III, IV + o Indeterminate				Total ulcers per stage per ICU per group /150 patients N (%) by cluster			

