	Care guide or policy Institutional Preventive (Yes-No) Name of guideline				N (%)			
	Professional Nurses per shift				Median ó mean (interquartile range IQR)			
	Auxiliares per shift				Median ó mean (interquartile range, IQR)			
**1–4 Months by ICU**	**T1√**	**T2√**	**T3√**	**T4√**	**T1√**	**T2√**	**T3√**	**T4√**
**6-Intervention Characteristic**	Adherence in ICU to intervention				Compliance day by day (yes = 1, no = 2) % compliance (calculated from 80% days stay per patient) ▪ Number of times one patient is mobilized in the intervention ▪ Description of the teams (total number of people who mobilized the patient) ▪ Total number of teams repeating intervention per shift ▪ The number of head and auxiliary nurses per team.			
	Acceptance of the final intervention of the study				Evaluation of the acceptability of the intervention by the personnel			
	Description of usual or conventional care by ICU				Descriptive Individual __or group__ Frequency per shift__ Position variation: yes_ No_ Descriptive.			

If by any chance (including medical assessment or clinical practice setbacks), patient mobilization is decided to be avoided, patients will be excluded from adherence to the intervention (temporarily or definitely), given the pragmatic nature of the study. This information will be registered on the platform. Regular follow-up will be ensured to verify if data is submitted completely and coherently. This will be done by the platform coordinator of PENFUP phase 2. When a pressure ulcer is detected, the nurse in charge of each patient will report it in the individual medical record and will assess the depth of each wound (Fig. 2. SPIRIT figure of study timeline).

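### The hypothesis (2-hourly versus every 4 h or slower) and the frequency-level aim do not match a control arm that is usual care at any frequency

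*Protocol article*

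**What the plan says.** The Background section describes the comparison in three ways that imply a fixed control frequency.

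- The hypothesis is that repositioning every 2 h or more often is more effective "than any other conventional repositioning (applied less frequently ≥ to every 4 h".
- The overall aim is to evaluate efficacy "on two frequency levels of repositioning or posture shifts in adult patients". The Abstract's Background states the objective in similar terms.
- The study is meant to resolve uncertainty "over what repositioning frequency in static patients best reduces PUs".

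The Methods define the control arm differently. Randomization and blinding describes it as "Intervention provided by care providers using a non-standardized frequency of repositioning". Control group B (conventional care) says: "Patients in this group will receive the usual care for repositioning applied at any frequency".

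Among the cluster criteria, the only repositioning interval named is on the slow side: Covid-19 units "in which the standard of repositioning is between every 12–16 h" are excluded.

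Other places already state the comparison as the intervention against conventional care: the Abstract's Methods, Study design, and numbered aims 1 and 2 in Background.

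Statistical analysis adds a process measure: the percentage of repositionings delivered out of those due, computed for both arms.

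**The concern.** A final report is read against its stated hypothesis. Here the hypothesis names a comparator (every 4 h or slower) that the control arm is not required to deliver. If control ICUs turn their patients more often than that, neither a positive nor a null result answers the question as worded. A null result could mean that 2-hourly turning is no better than 4-hourly turning, or that the control ICUs were already turning often. The wording invites the first reading. The Abstract's Conclusion expects the results to feed practice guidelines, so naming the wrong contrast could carry into recommendations.

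The same mismatch reaches the process measure. A percentage of the repositionings due needs a defined total. Usual care at any frequency sets none across the study, so the control-arm percentage would not show how far apart the two arms were in practice.

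**Working it through.** The point concerns definitions, so the check sets the statements side by side. No figure in the plan needs to be reproduced.

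**1. Which ICUs the control arm admits.** By their own practice, ICUs could fall into three groups:
- (a) every 4 h or slower;
- (b) between 2 h and 4 h;
- (c) every 2 h or more often.

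The hypothesis covers group (a) only. Control group B and Randomization and blinding admit all three.

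**2. Whether anything removes (b) and (c).** The cluster criteria under Inclusion and exclusion criteria concern adult critical care, a minimum of 10 beds, submission of the feasibility survey and commitment to the allocation. They exclude intermediate or coronary units with self-mobilizing patients, burn units, and the slow Covid-19 units. None removes an ICU because it turns patients often. Background reports that guidelines advise 2-hourly mobilization for patients with altered consciousness, though on low-graded evidence. Groups (b) and (c) are therefore possible on the protocol's own account. How common they are is not stated.

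**3. What the randomization estimates.** It compares ICUs told to reposition every 2 h with ICUs left to their own practice, averaged over whatever mix of (a), (b) and (c) they contain. This equals the hypothesized contrast only if (b) and (c) are empty, which nothing in the protocol ensures.

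**4. Whether it can show the best frequency.** Only one frequency is assigned. Ranking frequencies would need at least two assigned levels. Comparing ICUs by their own usual frequency is not a randomized comparison.

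**5. The process measure.** For the intervention arm, the Design of Intervention section sets a goal for shifts per 24 h, so a percentage of intended repositionings has a denominator. For the control arm there is no study-wide goal; at most, each ICU has its own protocol. The data needed to show separation are already planned: Data collection and procedure records daily shifts from patient charts in both groups and the total per patient in 24 h. Table 1 also has an item describing usual care in each ICU ("Frequency per shift__ Position variation: yes_ No").

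**The case against.** The strongest reply is that this is loose wording and not a design fault. The 4 h limit appears once, in a parenthesis in Background, and can be read as the authors' expectation of usual care. The Abstract's Methods, the Background sentence right after the hypothesis, numbered aims 1 and 2, and Study design all give the valid contrast. The Abstract's Conclusion and the Discussion make no claim about 2 h versus 4 h. Shifts per patient are already collected in both arms.

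Most of this stands. It confines the problem to the hypothesis, the overall aim, the best-frequency statement and the control-arm percentage. It does not remove the problem: an expectation written into the hypothesis and not enforced still leaves a hypothesis that the trial cannot test.

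A reader might infer more than the protocol supports:

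- **That the primary comparison is biased or the sample size wrong.** The planned control rate of 0.075 comes from the control group of the preceding phase 1 study and is not tied to any repositioning interval. The mismatch therefore does not show it, or any other planning figure, to be wrong.
- **That the planned effect is diluted by some given percentage.** This would need the share of control ICUs already turning often, and the protocol gives none.
- **That the intended contrast is 12 shifts a day against 6.** The intervention arm's minimum goal is 8 to 12 shifts in 24 h less 2 or 3 at night, so 12 cannot be assumed.
- **That usual-care frequency will be unknown before randomization.** The feasibility survey items are not shown, so this cannot be judged.

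**Conclusion.** The concern holds in a limited form. The hypothesis, the overall aim of two frequency levels and the best-frequency statement do not match a control arm defined as usual care at any frequency. The randomized comparison of a 2-hourly indication with usual care remains valid. What the design cannot support is a conclusion about 2 h versus 4 h or slower, or about the best frequency.

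The size cannot be quantified from the protocol, and the conclusion does not depend on a size. It rests on the definition of the control arm and on the eligibility criteria as printed. The point is more than clerical because it changes what the trial may claim. It calls for no change to eligibility, randomization, outcome, sample size or primary analysis.

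**What to change.** 1. In Background and the Abstract's objective, restate the hypothesis and overall aim as a 2-hourly repositioning indication versus usual care. Numbered aims 1 and 2 can stay.
2. Remove the promise to settle which frequency best reduces pressure ulcers.
3. Frame the trial's eventual conclusions as the same contrast.
4. In Statistical analysis, show separation between the arms by achieved shifts per patient per 24 h, by arm. Limit the percentage of intended repositionings to the intervention arm.

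The cost is protocol wording and one change of reporting measure. No new data are needed, because shifts are already recorded in both groups. The downside is a narrower claim: the trial will say whether a 2-hourly indication improves on current practice in these ICUs, and not how it compares with a specific slower interval.
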